### Other measures

Attitude towards online psychological intervention (Attitudes Towards Psychological Online Interventions Scale, APOI) [60]

The APOI questionnaire was used to determine the participants’ concerns regarding the adverse events, feasibility, professionalism, and effectiveness of online psychological treatments or interventions. More specifically, the APOI comprised 16 items categorized into four subscales, “confidence in effectiveness”, “doubt and risk perception”, “benefit of anonymity”, and “technology threat”. The subscales were scored on a 5-point Likert scale ranging from 1 to 5, specifying “completely disagree” to “completely agree.” Stronger levels of positive attitudes were denoted by higher “benefit of anonymity” and “confidence in effectiveness” subscale scores. Meanwhile, stronger levels of negative attitudes were noted with higher scores in “technological threats” and “doubt and risk perception.” The internal consistency coefficient of the questionnaire was 0.77 (0.62, 0.72, 0.64, and 0.62 for the four subscales, respectively).(2)Negative effects of the treatment (Negative Effects Questionnaire, NEO) [61]

The 20-item NEO was adopted to identify the adverse effects of the interventions. The respondents were interviewed about the occurrence of an adverse event (yes/no), the strength or extent of the effect (0 to 4), and whether the side effect was attributable to the intervention or other causes. Accordingly, two scores were acquired: the extent of the adverse effects (0 to 80) and the frequency of treatment-related reactions (0 to 20). The internal consistency coefficient of the questionnaire was 0.95.(3)Credibility and expectancy (Credibility/Expectancy Questionnaire, CEQ) [62]

The credibility subscale assessed beliefs about the treatment’s effects, while the expectation subscale evaluated the extent to which the participants felt that their symptoms improved during the intervention. This 6-item questionnaire had an internal consistency coefficient of 0.84.(4)Satisfaction

At the end of every module, the following four open-ended questions were asked to measure user satisfaction:Were some parts helpful or reassuring?Did some parts make you feel worthless or evoke complex emotions?For family members or friends experiencing challenges similar to yours, would you recommend this module?On a scale of 1 to 10, how valuable was this module?(5)Compliance

The learning behaviour profile on the Moodle platform was used to measure patient compliance, including the number and dates of participant logins to the online intervention, the number of modules completed, the number of exercises completed, and the total time expended on the modules and exercises. In the study assessment, 6 and 12 weeks later, the intervention group participants were interviewed about their frequency of use of the intervention.

## Safety

Based on the findings of similar studies, we anticipate minimum risk of adverse events and serious adverse events in the study. When the participants would report the negative effects, the author will help them to get help from professional advisors. All adverse events will be treated, recorded in detail, and reported to the Research Ethics Committee immediately.

## Data monitoring

Data will be collected and managed by a researcher. All the data will be stored in hard drives. The Ethics Committee who is independent from the sponsor and competing interests will supervise this trial and will make the final decision to terminate the trial. The project management group will meet every month.

## Data analysis

The four-part statistical analysis of this paper comprises (a) descriptive statistics, (b) the main outcome’s confirmatory analysis with a sensitivity analysis, (c) secondary outcomes and their assessment with a sensitivity analysis, and (d) an adjustment effects analysis. All statistical analyses were performed using SPSS.

### Additional analyses

The additional analyses included the assessment of potential moderators or confounding variables. Therefore, potential pre-intervention differences in IPS were examined along with the demographic variables between the experimental and control groups by performing independent samples *t* tests. For the intervention × time interaction, these variables were included as moderators to verify the stability of the findings when the two groups were significantly different. The primary outcome could have been affected by the covariates, including emotion regulation, the participant’s stance regarding internet-based psychological interventions, patient satisfaction and adherence, and expected patient outcomes, which were added to the analysis.

Additionally, weekly assessments of procrastination were analysed, allowing us to measure changes in procrastination with higher ecological validity and temporal resolution. In the intervention group, we investigated the percentage of side effects encountered due to the treatment and calculated the degree of damage resulting from these effects. Moreover, the subjects’ self-control, self-efficacy, and time management strategies in their daily lives may be potential moderators or mediators of procrastination reduction.

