### Measures

The results included questionnaires and learning behaviour data. Assessments were repeated at baseline, 6 weeks, and 12 weeks. Table 2 provides an overview of the measurements including the schedule of measures and the timelines.

**Table 2 Tab2:** Schedule of measures and timelines

	Enrolment	Baseline	Every 2 weeks (only intervention group on)	Mid-treatment	Post-treatment
Enrolment - Eligibility screen - Informed consent	×				
Demographic variables - Gender - Age - Education - Marriage - Courses - Semester - Psychotherapy experience - Income - Job - Email - Phone number	×				
*Primary confirmatory outcome*					
Procrastination (IPS)	×		×	×	×
Procrastination (PPS)		×	×	×	×
*Secondary confirmatory outcome*					
Depression (PHQ-9)		×	×	×	×
Anxiety (GAD-7)		×	×	×	×
Stress (PSS-10)		×	×	×	×
Well-being (WHO-5)		×	×	×	×
*Secondary exploratory outcome*					
Learning self-efficacy (SSE)					×
Self-control (SCS)					×
Cognitive emotion regulation (CERQ)					×
Time management strategy (MSLQ-B)					×
*Other measures*					
Attitudes towards online intervention (APOI)				×	×
Risk and side effects (NEO)				×	×
Credibility (CEQ)				×	×
Satisfaction				×	×
Special time period - Taking an exam - On vacation				×	×
Changes in other treatments				×	×
Usability (module understanding, use, benefit)			×		
User learning behaviour data - User login - Complete the module - Complete the questionnaire - Finish homework - Complete the event - Time to read text - Time to practice - Number of clicks			×	×	×

*Note: IPS* Irrational Procrastination Scale, *PPS* Pure Procrastination Scale, *PHQ-9* Patient Health Questionnaire-9, *GAD-7* General Anxiety Disorder-7, *PSS-10* Perceived Stress Scale (PSS-10), *WHO-5* The World Health Organization-Five Well-Being Index, *SSE* Student Self-efficacy Scale, *SCS* Self-Control Scale, *CERQ* Cognitive Emotion Regulation Questionnaire, *MSLQ-B* Motivated Strategies for Learning Questionnaire part-B for distance learning, *APOI* Attitudes towards Psychological Online Interventions, *NEO* Negative Effects Questionnaire, *CEQ* Credibility/Expectancy Questionnaire

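### The additional adjusted analyses of the primary outcome use covariates that the schedule places only after randomisation, two of which do not exist in the waitlist arm

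*Protocol article*

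**What the plan says.** The Additional analyses section opens by stating its scope: "The additional analyses included the assessment of potential moderators or confounding variables". It describes checking baseline differences and entering differing variables into the intervention-by-time model to see whether the findings are stable. It then continues: "The primary outcome could have been affected by the covariates, including emotion regulation, the participant’s stance regarding internet-based psychological interventions", and closes the list with "patient satisfaction and adherence, and expected patient outcomes, which were added to the analysis". So five variables are called covariates of the primary outcome and are entered in a model.

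The timing of each is in Table 2 (Measures) and the text on measures:

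- **Emotion regulation (CERQ):** one mark, at post-treatment.
- **Attitude (APOI), expectancy (CEQ), satisfaction:** marks at mid- and post-treatment only. The text adds that satisfaction is asked at the end of each module.
- **Adherence:** "The learning behaviour profile on the Moodle platform was used to measure patient compliance". Table 2 marks learning behaviour data in the two-weekly column (intervention group only) and at mid- and post-treatment.

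The Control condition section states that the waitlist arm has no access to the programme during the 12-week assessment period.

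**The concern.** A covariate measured before randomisation cannot be affected by treatment, so adjusting for it leaves the randomised comparison intact. These five variables, as scheduled, can be affected by treatment.

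Emotion regulation is the subject of Module 4 in Table 1 and a listed secondary outcome, so it is an intended route of the effect. The CEQ expectancy subscale is described as "the extent to which the participants felt that their symptoms improved during the intervention", which is close to the outcome itself. Satisfaction and adherence describe use of a programme that one arm does not have.

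Such variables cannot confound a randomised comparison. Conditioning on them removes part of the effect or introduces bias through shared causes. Because the section presents its adjustments partly as a check on stability, a real effect could appear to vanish in the adjusted model and be reported as not robust.

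**Working it through.** **Inputs.** From the sample size paragraph (under Interim analyses): means 4.96 and 2.96, so a difference of 2.00; SD 5.5; alpha 0.05; total 320, or 160 per arm. Power and sidedness are not stated; I assume two-sided 90%.

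**The plan's own figure.** n per arm = 2 × (1.960 + 1.282)² × 5.5² / 2.0² = 158.9, rounded up to 159, or 318 in total. This agrees with 320. With 160 per arm, SE = 5.5 × √(2/160) = 0.615 and power = 0.90. The point does not depend on this figure, but it fixes the scale.

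**Covariates that could be collected in both arms (CERQ, APOI, CEQ).** Two mechanisms, with assumed values because the documents give none:

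1. *Mediation.* If a share s of the effect runs through the covariate and nothing else links the two, the adjusted effect is 2.0 × (1 − s). Power is approximated with the SE held at 0.615.

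| Share s (assumed) | Adjusted effect | Power |
|---|---|---|
| 0% | 2.0 | 0.90 |
| 25% | 1.5 | 0.68 |
| 50% | 1.0 | 0.37 |
| 75% | 0.5 | 0.13 |

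A 1,000-replicate simulation that fitted the adjusted model gave effects of 1.98, 1.49, 1.01 and 0.48, with rejection rates of 87%, 65%, 41% and 15%. The simulation re-estimates the SE under adjustment, whereas the formula keeps it fixed. At s = 50% this gives the range 37–41%.

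2. *Shared unmeasured cause, nothing mediated.* Suppose treatment shifts the covariate by 0.4 SD, and an unmeasured factor affects covariate and outcome with loading u. The adjusted effect is 2.0 − 0.4 × 5.5 × u². For u = 0.3 it is 2.0 − 0.20 = 1.80; for u = 0.5 it is 2.0 − 0.55 = 1.45. So bias arises even when the covariate carries none of the effect. With 75% mediated and u = 0.5, the adjusted effect is about zero.

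**Covariates that exist in one arm only (satisfaction, adherence).**

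- *Left missing for controls.* Complete-case analysis drops all 160 controls. Only treated rows remain, so the arm indicator equals the intercept. The design matrix (intercept, arm, covariate) has rank 2 of 3, and the arm effect cannot be estimated. This needs no assumed effect size.
- *Coded 0 for controls.* The arm coefficient compares controls with treated participants extrapolated to zero use. Its SE is 5.5 × √(1/160 + 1/160 + Ā²/Σ(A − Ā)²), where A is modules completed in the intervention arm. Under an assumed uniform spread of 1–7 modules (mean 4, variance 4) this is 5.5 × √(0.0125 + 16/640) = 1.07; one simulated data set gave 1.10. Under 3–7 modules (mean 5, variance 2) it is 5.5 × √(0.0125 + 25/320) = 1.66; simulation gave 1.62. Both compare with 0.615 unadjusted. If the benefit also accrues per module (assumed 0.4 per module), the arm coefficient is about zero (0.03 in simulation).

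**The case against.** **A reader might infer that the headline primary result is biased.** The documents do not support this. The Primary and secondary outcome analyses section specifies the repeated-measures mixed model and names none of these covariates. The Data analysis section lists the confirmatory analysis separately from an adjustment effects analysis. The problem lies in the additional analyses only.

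**A reader might also infer that every adjusted estimate is not estimable.** That fits only satisfaction and adherence, and only in a two-arm model. For CERQ, APOI and CEQ the problem is bias for the total effect.

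**The timing may be a table error.** The Measures section says in general that assessments were repeated at baseline, 6 and 12 weeks. The strengths section speaks of changes in time management and self-control, which carry the same single post-treatment mark as the CERQ. This has some force for the CERQ: a baseline score, if collected, would be a legitimate covariate. But the item-level schedule shows none, and the argument does not rescue satisfaction or adherence.

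**The purpose is open.** The sentence does not say which coefficient is interpreted, and the article declares an interest in moderators, mediators and mechanisms. Conditioning on a mediator is not wrong if the result is labelled a direct effect. This stands in part, and it is why a blanket ban on these variables would go too far. Yet the sentence calls them covariates; it is self-control, self-efficacy and time management that are named separately as possible moderators or mediators.

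**The magnitudes are assumed.** This stands: mediated shares, loadings, module counts and zero coding are not in the documents. The calculations also use a single time point rather than the planned repeated-measures model.

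**Conclusion.** The concern holds for the additional adjusted analyses of the primary outcome. As scheduled in Table 2, none of the five covariates is a pre-randomisation variable. For CERQ, APOI and CEQ, the adjusted coefficient is biased as an estimate of the total effect. The size is unknown: 2.0 becomes about 1.0, with power about 37–41% rather than 90%, under an assumed 50% mediated share, and 1.5 to 0.5 across shares of 25–75%. For satisfaction and adherence, the loss of estimability with complete cases follows from the design alone. With controls coded 0, the coefficient no longer answers the trial's question, and its SE rises to between 1.07 and 1.66 under the spreads tried. The confirmatory mixed model and the sample size are not shown to be affected.

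**What to change.** 1. State that any model reported as estimating the treatment effect adjusts only for variables measured before randomisation.
2. Analyse satisfaction, adherence and expectancy descriptively, or as predictors of outcome, within the intervention arm.
3. Move emotion regulation to an explicitly labelled exploratory mediation analysis with its assumptions stated, so that it is not presented as an adjusted or stability check of the primary result. This keeps the mechanism aims that the article declares.
4. Apply rule 1 to attitude (APOI) as well: as scheduled, it should not be an adjustment covariate.
5. Reconcile the general statement on baseline assessments with Table 2, item by item. If the CERQ was collected at baseline, say so; that score may then be used as a covariate.

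The cost is wording; no sample size or visit changes. Adding APOI or CEQ at baseline is not a simple remedy. Under Trial status the study is already recruiting, so those enrolled earlier would lack the measure. The CEQ expectancy subscale, as the article describes it, also asks about improvement felt during the intervention, which has no meaning at baseline.

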### Control condition

Individuals assigned to the waitlist control group did not have access to the online-based intervention during the 12-week assessment period. After completing their final assessment, they received an email with an access link for the intervention. Throughout the study period, participants in both groups could receive other treatments, and such treatments were measured at every evaluation.

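### Side effects are summarised in the intervention group only and by self-attribution, so the harm conclusion makes no use of the randomised control; a by-arm analysis of individual worsening would cheaply mend this

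*Protocol article*

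**What the plan says.** Under Additional analyses, the article states: "In the intervention group, we investigated the percentage of side effects encountered due to the treatment". The degree of damage from these effects is summarised for the same group.

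Other measures describes the instrument, the Negative Effects Questionnaire (NEO in the article). It has 20 items and asks whether an event occurred, how strong it was, and "whether the side effect was attributable to the intervention or other causes". Two scores follow: "the extent of the adverse effects (0 to 80) and the frequency of treatment-related reactions (0 to 20").

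Table 2 (Measures) ticks the row "Risk and side effects (NEO") at mid-treatment and post-treatment. Only one column of that table carries an arm restriction, "Every 2 weeks (only intervention group on"), and the questionnaire is not ticked in it. PHQ-9 and GAD-7 are ticked at baseline, mid-treatment and post-treatment.

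Under Control condition, the waitlist group "did not have access to the online-based intervention during the 12-week assessment period", and "participants in both groups could receive other treatments". The Safety section adds: "All adverse events will be treated, recorded in detail, and reported to the Research Ethics Committee immediately". It names no arm and no comparison.

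**The concern.** The trial has a concurrent, randomised, untreated control group, which is the natural yardstick for harm. The stated analysis sets it aside. What remains is a percentage in one arm, filtered by the judgement of participants who know that they have the programme.

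That judgement can err both ways. Low mood or stress during a term may be blamed on the programme, or a real deterioration may be put down to exams or another treatment. Table 2 records exam periods, vacations and changes in other treatments, so the authors themselves expect such influences.

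The Discussion lists possible adverse effects and risks among the things the trial will study. Followed as written, the plan gives a figure that does not say how much worse off, if at all, anyone is than without the programme.

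**Working it through.** **Stated figures.** The article gives no expected side-effect rate and no precision for a harm comparison, so there is no harm figure to reproduce. The only planning number used here is 160 per arm (Abstract).

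**What the attributed percentage measures.** Let B be the background event rate, E the excess caused by the programme, m the share of background events wrongly attributed to the programme, and s the share of excess events correctly attributed. Ignoring overlap, the attributed rate is approximately

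A = s × E + m × B.

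The intervention arm supplies A. It does not supply s, m, B or E separately. If E = 0 and B = 20% (assumption), A lies anywhere from 0% (m = 0) to 20% (m = 1). If E = 10 points, the first term alone lies anywhere from 0 to 10 points as s runs from 0 to 1. So A carries some information, but E cannot be recovered from it.

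**What a two-arm comparison adds.** Take an outcome with no attribution filter, such as worsening on PHQ-9, and suppose that 20% of the intervention arm meet it. The one-arm half-width is 1.96 × √(0.20 × 0.80 / 160) = 6.2 points. That same 20% is compatible with each row below. The rates are assumptions, and the half-width of the difference is 1.96 × √[p₁(1−p₁)/160 + p₀(1−p₀)/160].

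| Control rate p₀ | Intervention rate p₁ | Risk difference | Half-width |
|---|---|---|---|
| 20% | 20% | 0 points | 8.8 |
| 10% | 20% | 10 points | 7.7 |
| 5% | 20% | 15 points | 7.1 |

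**Precision, with and without dropout.** With equal rates p in both arms, the half-width is 1.96 × √[2p(1−p)/n]. An assumed loss of 30% leaves 0.7 × 160 = 112 per arm.

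| p (assumed) | n = 160 per arm | n = 112 per arm |
|---|---|---|
| 5% | 4.8 points | 5.7 points |
| 20% | 8.8 points | 10.5 points |
| 30% | 10.0 points | 12.0 points |

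With 160 per arm fully observed, power for a 10-point excess is 0.85, 0.71, 0.54 and 0.47 at background rates of 5%, 10%, 20% and 30%. Estimates with intervals are therefore more honest than tests.

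**Are the data there in both arms?** For PHQ-9 and GAD-7, yes. Table 2 schedules them without arm restriction, and the end of the Background says that depression and anxiety, among others, are compared with the control group. For the questionnaire this is not settled. Its ticks carry no restriction, but Table 2 also ticks satisfaction and learning-behaviour data at mid- and post-treatment. Other measures asks satisfaction after each module, and controls have no programme access in that period.

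**The case against.** The strongest reply is that the planned sentence is not wrong in itself. Effects attributed to the treatment have no counterpart in an untreated waitlist, so describing them in the intervention arm is sensible. This stands, and the fix keeps that summary.

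The second reply is that a by-arm adverse-event table and a reliable-change threshold commonly belong to an analysis plan that is not shown, and that nothing in the Safety section rules out such a table. This has some force for the details. It does not remove the point, because the article fixes the population and the attribution rule of the one side-effect analysis that it states.

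The third reply is that mean depression, anxiety and well-being are already compared between arms. True, but a mean can stay level or improve while a minority deteriorates.

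Three stronger readings are tempting, and the documents do not support them:

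- A reader might infer that excess harm cannot be told from background events at all. The attribution item gives some separation, although not the excess over control.
- A reader might infer that the by-arm comparison of the questionnaire is already in the data and would settle the matter. Table 2 does not show that controls complete it, and the precision above would not settle a modest excess.
- A reader might infer that if 20% to 30% of controls report an event, the plan would report 20% to 30% side effects with no excess. That needs every background event to be attributed to the programme (m = 1), whereas the plan counts only attributed effects.

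**Conclusion.** The point holds as a cheap improvement. The only stated side-effect analysis is one-armed and self-attributed, and no by-arm analysis of harm or individual worsening is stated. The harm conclusion therefore does not use the randomised control and does not identify the excess.

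No numerical bias can be claimed, because the article gives no event rates. The half-widths of 4.8 to 10.0 points rest on assumed rates of 5% to 30%, equal in both arms, and on 160 per arm fully observed. The article itself expects high dropout; at an assumed 30% loss they widen to between 5.7 and 12.0 points. The matter concerns secondary safety reporting and leaves the primary efficacy result untouched.

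**What to change.** 1. Keep the treatment-attributed summary and label it as a description of the intervention arm.
2. Add, by arm, the proportion worsening from baseline on PHQ-9 and, separately, on GAD-7 by a pre-set reliable-change amount at weeks 6 and 12, with risk difference and 95% confidence interval. Fix the amount before the data are unmasked. One option is 1.96 × SD × √[2(1−r)]. With the article's internal consistency coefficients this is 1.96 × √0.36 = 1.18 SD for PHQ-9 (r = 0.82) and 1.96 × √0.22 = 0.92 SD for GAD-7 (r = 0.89), where SD is the baseline standard deviation.
3. State whether controls complete the negative-effects questionnaire. If they do, also report occurrence and extent by arm regardless of attribution. If they do not, step 2 still stands.
4. Give the number observed in each arm at each time point, and present estimates with intervals, not tests.

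The cost is one extra table from assessments already scheduled in both arms. The drawback is limited precision, which the intervals will show.

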## Discussion

Preliminary indications from several studies have revealed that internet-based interventions targeting procrastination are acceptable [3]. However, few relevant evidence-based studies have been conducted, with inconsistent quantification methods for procrastination and limited long-term follow-up studies. Further research on the efficacy of internet-based interventions for procrastination is necessary. The research findings in this paper are expected to contribute to and advance the literature on online-based psychological interventions. Equally important, the results have crucial implications for the therapeutic management of procrastination among adults. The findings presented are also anticipated to mitigate the severity of procrastination among the subjects and improve their quality of life.

This RCT was designed to investigate the efficacy of a 12-week online-based intervention on procrastination in adults. The primary and secondary outcomes of this study compared the intervention and alternate control groups in the context of their respective levels of procrastination. This approach adds high-quality, sufficiently robust evidence to the weak research base for CBT-and internet-based procrastination interventions. We will also study the acceptability of the intervention design, including potential adverse effects and risks, adherence, and intervention satisfaction, to further refine the intervention design. Additionally, we will explore potential moderators and mediators to understand how the intervention works and who might be more valuable.

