### Strengths and limitations of this study

With the aim of maximizing the internal validity of our findings, the design of this study as an RCT with a waitlist control group was based on our objective to assess the efficacy of online-based interventions. Our randomization approach abides by the principle of sequential allocation concealment to further lessen the systematic bias. In addition, those who procrastinated on medication or psychotherapy at baseline were excluded to minimize systematic pre-treatment differences.

In addition to investigating the changes in procrastination-related behaviours, we examined how participants benefited from online-based interventions in their daily lives. Since procrastination is linked to a broad spectrum of adverse outcomes, evaluating the changes in one’s work ability, well-being, and psychosocial functioning will aid in assessing online-based interventions from a holistic perspective. Additionally, our study investigated the possible mechanisms of various changes, such as changes in self-esteem, time management, and self-control, which may help advance the precision of procrastination interventions in the future.

However, these advantages may also come with some limitations. First, to achieve the power of statistical analysis, a large number of participants was required, and recruiting such high numbers of participants can be challenging because the proportion of the general population with severe procrastination behaviours is relatively low, as is the number of those seeking help. Certain barriers could limit the number of interested and eligible participants. We used various recruitment strategies, such as offline and online advertising, and allowed participation independent of the subjects’ location.

The second challenges are the study’s high discontinuation rate and low adherence. The latter challenge is particularly concerning in our case because a considerable number of evaluations that merge online-based interventions with standard questionnaires will yield relatively high participation rates among the patients. We provided reminders via phone calls, emails, and text messages to improve compliance. Moreover, our assessment scales were kept as short as possible, incorporating subscales only when necessary. An intention-to-treat method was adopted, and sensitivity analysis was performed for the data analysis to measure the impact of potential dropouts.

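### Table 2 schedules self-efficacy, self-control, emotion regulation and time management at post-treatment only, against the text; as printed, it cannot support the moderator, mediator and change claims

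*Protocol article*

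**What the plan says.** All references are to the protocol article.

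- **Measures, text:** "Assessments were repeated at baseline, 6 weeks, and 12 weeks". No scale is excepted.
- **Measures, Table 2:** the rows beginning "Learning self-efficacy (SSE", "Self-control (SCS", "Cognitive emotion regulation (CERQ" and "Time management strategy (MSLQ-B" each carry one mark, in the post-treatment column.
- **Additional analyses:** "self-control, self-efficacy, and time management strategies in their daily lives may be potential moderators or mediators of procrastination reduction". The same section adds emotion regulation to the analysis as a covariate that could have affected the primary outcome.
- **Discussion:** "we will explore potential moderators and mediators to understand how the intervention works".
- **Strengths and limitations of this study:** "our study investigated the possible mechanisms of various changes, such as changes in self-esteem, time management, and self-control".

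**The concern.** A moderator has to be fixed before randomisation, because a score taken after treatment may itself have been changed by treatment. Here that is expected: Table 1 includes modules on goal and time management and on emotion regulation. A change score needs two readings. A mediator needs to come before the outcome it is said to explain, and needs baseline values of mediator and outcome so that pre-existing correlation is not mistaken for mechanism. One reading taken alongside post-treatment IPS meets none of these conditions. Lower procrastination could equally have produced better self-control.

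The study of mechanisms is an announced aim and a claimed strength. No later analysis plan can recover baseline readings that were never taken. The CERQ raises a separate issue that reaches the primary outcome: a post-treatment score used as a covariate is a post-randomisation variable, and adjusting for it can distort the estimated treatment effect.

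**Working it through.** **1. Readings per scale in Table 2**

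- IPS: enrolment, every 2 weeks (intervention group only), mid-treatment, post-treatment = 4 marks.
- PPS, PHQ-9, GAD-7, PSS-10, WHO-5: baseline, every 2 weeks (intervention group only), mid-treatment, post-treatment = 4 marks each.
- SSE, SCS, CERQ, MSLQ-B: post-treatment = 1 mark each.

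The neighbouring rows fall cleanly into their columns, so a damaged table is an unlikely explanation. Even a displaced mark would still be a single reading.

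**2. What each analysis needs, and what Table 2 supplies**

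- Moderator (SSE, SCS, MSLQ-B): needs a pre-randomisation value. None is scheduled.
- Change: needs at least two readings. One is scheduled.
- Mediator: needs a reading before the outcome, with baseline adjustment. The only reading coincides with post-treatment IPS, and there is no baseline.
- Covariate (CERQ): needs a pre-randomisation value. The only one is post-randomisation.

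**3. How far a post-only mediator can mislead**

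The documents give no correlations, so all inputs here are assumptions. Mediator and outcome have variance 1 within arm. Their baseline correlation is −r, with r = 0.3 or 0.5. Each has stability s = 0.5 or 0.7 from baseline to post-treatment. Treatment shifts each by 0.4 SD in the favourable direction. The mediator has no effect on the outcome.

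- Treatment to mediator: a = 0.4.
- Mediator to outcome given arm, post-only: b = −r × s².
- Apparent share of the total effect: (a × b) / (−0.4) = r × s².

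Results:

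- r = 0.3, s = 0.5: 0.3 × 0.25 = 7.5%
- r = 0.3, s = 0.7: 0.3 × 0.49 = 14.7%
- r = 0.5, s = 0.5: 0.5 × 0.25 = 12.5%
- r = 0.5, s = 0.7: 0.5 × 0.49 = 24.5%

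A simulation of 400,000 participants per scenario gave 7.5%, 14.7%, 12.7% and 24.1%. With baseline mediator and outcome in the model, the spurious indirect effect was within 0.001 of zero in every scenario.

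**4. Precision of the between-arm comparison**

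The variance of a baseline-adjusted comparison relative to a post-only one is 1 − r², where r is now the assumed baseline-to-post correlation of the scale. The reduction forgone is r²: 0.3² = 9%, 0.5² = 25%, 0.6² = 36%. The low end matters, because SSE has a stated internal consistency of only 0.66 and the MSLQ-B subscale has three items.

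**The case against.** **The schedule may not be once-only.** A reader might infer from Table 2 that post-treatment-only measurement is settled. The documents do not support that. The Measures text implies baseline and week-6 readings. The table and text also disagree elsewhere about these same four scales: Table 2 calls them secondary exploratory, while the section describing them is headed as secondary confirmatory. Table 2 may be the error. This stands, and it is why the point is first a contradiction to be reconciled.

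**The analyses may not be impossible.** A reader might infer that nothing can be done with the four scales. That goes too far. A post-treatment comparison between randomised arms is valid, and a cross-sectional mediation model can be fitted. What fails is the interpretation.

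**Week 18 might supply the time order.** Methods/design lists a week-18 assessment (T3), so a week-12 mediator could precede week-18 IPS. But Table 2 has no such column, and by the Abstract and Control condition week 18 falls after controls receive access. Randomization and blinding instead tells waitlist participants that the start comes after 18 weeks, so the documents conflict on this too. Under either reading the mediator has no baseline.

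**The mixed model.** A reader might infer that the repeated-measures model and within-group effect sizes under Primary and secondary outcome analyses are promised for these scales and must fail. The heading covers secondary outcomes, but the text explicitly ties the model only to procrastination, so this is not part of the point.

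**Emotion regulation as a mediator.** A reader might group the CERQ with the mediators. Additional analyses names it only as a covariate, and the list of mechanisms under Strengths and limitations omits it. Its problem is post-randomisation adjustment.

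**Exploratory intent.** Additional analyses and the Discussion use tentative wording. That lowers the stakes, but Strengths and limitations presents the mechanism work as done. Exploratory analyses still need data that can bear on the question.

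**Conclusion.** The point holds in this form. Table 2 and the Measures text contradict each other for SSE, SCS, CERQ and MSLQ-B. If Table 2 governs, none of the three scales named as moderators or mediators has a pre-randomisation value, a change score or a baseline-adjusted reading that precedes post-treatment IPS. Adjusting the primary outcome for CERQ would then be adjustment for a post-randomisation variable.

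The schedule count is exact. The sizes are illustrative: a spurious mediated share of about 7.5% to 24%, and a forgone variance reduction of 9% to 36%, both resting on assumed correlations. An unadjusted comparison of the primary outcome between arms is not affected.

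**What to change.** Reconcile Table 2 with the Measures text. If the scales were given at baseline and week 6, correct the table. If not:

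- Schedule SSE (10 items), SCS (19) and MSLQ-B (3) at baseline and week 6, and CERQ (36) at least at baseline, in both arms.
- Use baseline values as moderators or covariates, and baseline-adjusted week-6 values as mediators of week-12 IPS.

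The cost is 10 + 19 + 3 = 32 online items at each of two existing time points, plus 36 at baseline: 68 at baseline and 32 at week 6, or 100 per participant. The drawback is response burden, which Strengths and limitations already acknowledges.

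If baseline has passed or the burden is refused, the change is to wording and analysis only:

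- Report the four scales as post-treatment between-arm comparisons.
- Withdraw the moderator, mediator and mechanism-of-change claims for these scales in Additional analyses, Discussion and Strengths and limitations.
- Do not adjust the primary outcome for post-treatment CERQ.
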